#### *Ethical Considerations for Venue Visits and Mapping*

Because knowledgeable people interviewed at venues are only asked questions about the venue and not about their personal behavior, there is no personal risk involved in this phase of data collection. No personal identifying information is collected from the respondent.

Maps made using the data from this phase of data collection will not indicate the location of vulnerable populations such as sex workers, MSM and transgender women. Venue maps will only indicate the distribution of venues and the coverage of prevention programs. Maps of priority venues for interventions may include venues where sex workers, MSM and transgender women visit, however the presence of specific populations will not be indicated.

#### *Consent Process for Venue Visits and Mapping*

Interviewers will explain to **site informants** the purpose of the study, type of questions asked, and that no identifying information will be collected from them. Site informants will not require formal consent as the data collected from these informants is unrelated to their personal characteristics and is centered on the PPA and/or venue of interest. Site informants will receive a fact sheet about the study will contact number for the local and UNC researchers.

Knowledgeable people at venues are not asked any personal information. They are asked their age in order to confirm eligibility (age 18 or older are eligible). Once eligibility is determined, the interviewer will read a short description of the study and the type of questions that will be asked.

*“Hello. My name is \_\_\_\_\_ and I am working with Tchikos/the National Institute against HIV/AIDS the national on a study that will improve HIV prevention programs here. I would like to ask you some questions about this place to find out about people who come here to socialize or meet sex partners and about HIV prevention that has occurred here. I can offer you this Fact Sheet that has more information about the study.”*

The interviewer will offer the respondent a Fact Sheet (see Appendix 8) that contains information about the study, including contact information within Angola in case questions arrive after the interview. Next, the interviewer asks if they are willing to participate. If they are willing, the interview begins.

#### ***Step 4: Key population interviews among site workers and patrons; HIV, CD4 and STI testing Selection of Sites and Events for Worker and Patron Surveys and Testing***

Individual interviews and HIV testing with male and sex workers, men who have sex with men and transgender women will be performed in a sample of sites and events visited in the previous step. Social mobilizers will assist interviewers in identifying sex workers, men who have sex with men and transgender women at venues. At venues where social mobilizers accompany interview teams, all people identified by social mobilizers as potentially people from key populations will be interviewed. Additionally, people at venues will be approached randomly by interviewers and will not be screened for eligibility based on history of sex worker or same-sex practices. Through random selection, some participants may not be sex workers, MSM or transgender people.

Sites will be selected using a systematic fixed-interval sampling strategy with the probability of selection proportional to the size of the site. The size of a site is defined by the number of people socializing at the venue during a busy time as reported by the site informant. A sampling frame of sites that were confirmed to exist and be in operation and those that were temporarily closed during site visits (Step 3) will be constructed, with sites and events sorted by province/geographic area, type and size. Prior to interval selection, venues eligible for individual interviews are sorted by geographic location, as indicated by geographic code, and size of venue.

#### *Inclusion Criteria for PLACE*

Male and female participants who meet the following eligibility criteria will be invited to participate in the project:

- At least 15 years of age at time of interview and not accompanying or running an errand for parents
- Recruited at selected venues
- Consent to participant in a face-to-face structured behavioral survey and provide written informed consent with initials or an X

Additionally participants that meet one of the following inclusion criteria for key populations will be offered additional STI testing:

- At least one sexual contact for cash in the last 12 months
- Man or transgender woman that has had oral or anal sex with another man in the past 12 months
- Identification as a male-to-female transgender woman

#### *Recruitment of sex workers, men who have sex with men and transgender women at venues*

In this step, trained interviewers visit the sampled sites and events to interview eligible and consenting key populations present at that time. The team of survey interviewers will be accompanied by a team of people from the district health office trained in HIV counseling and testing.

Upon arrival, a field supervisor will speak with the person in charge of the site and explain the study and HIV testing that will be offered free of charge to participants. They will ask permission to begin requesting the participation of workers and patrons. It may be necessary to visit the venue at a time that the workers are less busy, for example in late afternoon or early evening before patrons arrive for an evening of socializing.

After being informed about the survey and testing, patrons and workers will be asked to participate. Social mobilizers will assist interviews in recruitment of patrons and workers who are from key populations. As most venues are expected to be small, all patrons and workers will be approached to participate. If more patrons or workers are present at a given site than can be feasibly interviewed in the time allotted to field staff, a systematic sample of patrons and a systematic sample of workers will be approached and asked to participate. If a patron or worker does not agree to be tested for HIV, the interview will not be carried out. The patron or worker will be screened for age eligibility. Persons who do not meet the inclusion criteria will not be interviewed. The respondent may be asked to move to an area of the site or near the site in order to preserve

privacy of responses. Once a respondent finishes the interview, they will be brought to the HIV counselors for testing and counseling.

The interviewer will use a structured questionnaire on a smartphone to interview respondents (see Appendix 4). The interview will take 20 to 30 minutes and the testing and counseling will require extra time. The survey instrument includes questions about socio-demographic information, sexual behavior, and exposure to HIV prevention programs. With participants of sufficient literacy, a portion of the sensitive questions about sexual behavior will be administered with the interviewer reading the questions and the respondent marking answers on a separate pre-printed answer sheet that will then be placed in an envelope without the interviewer seeing the responses. Either electronic data collection tools, i.e. mobile phones/tablets, or paper forms will be used to interview site workers, patrons and key populations.

There is one questionnaire used in this step (Appendix 4):

- Form C: Patron and Worker Questionnaire – obtains sociodemographic characteristics of the individual being interviewed, their sexual history and behavior, and prior exposure to HIV testing/prevention activities.

HIV testing will be conducted independently in or near the venue by a trained counselor and tester from the District Health Team. The HIV testing and counseling provided will include a rapid HIV test (using a blood spot from a finger prick) and the standard national counseling protocol, including pre- and post-test counseling (Determine HIV 1/2, Alere/Abbott, Waltham, MA, USA and Unigold HIV, Trinity Biotech, Bray, Ireland). Any person testing positive will be asked to give another drop of blood for a confirmatory HIV test. In the case of conflicting results from the two tests, a third test will be done on site. HIV test results will be provided on site along with post-test counseling. Counselors will follow up with participants testing positive for HIV to link them to additional health services in accordance with national guidelines.

Finger-prick blood samples will be collected to measure the CD4 T-cell count of HIV-positive participants using a rapid CD4 T-cell count analyzer, such as the PIMA Analyzer (Alere, Waltham, MA, USA). Based on the results of the CD4 test, patients will be referred to appropriate ART clinics for medical care and treatment. Venous blood will be collected from HIV positive consenting participants for posterior viral load quantification using Xpert Viral Load or PCR. Dried blood spots (DBS) will be collected for all consented participants. Samples will be collected by trained project staff. Participants will receive a finger stick to obtain blood sample according to the methods described in the Abbott DBS Collection Reference Guide (Abbott Laboratories, Abbott Park, IL, USA). Samples will be transported to a central laboratory site for quantitative viral load assay. All specimens must be processed within seven days of receipt at laboratory. Remaining samples will be stored at the testing laboratories in gas-impermeable zip closure storage bags in an -80C freezer for additional testing, as funding becomes available. Participants will be informed of their viral load results within one month of testing.

Men and women identified as at increased risk based on the interview will be offered additional STI testing. People who have been paid for sex or men who have had sex with other men in the past 12 months will be offered testing for syphilis, hepatitis B, gonorrhea, chlamydia and trichomoniasis. Syphilis and Hepatitis B serologic testing will be conducted using finger stick blood and an onsite rapid test. In addition, women will be asked to provide a self-collected vaginal specimen and men will be asked to provide a urine sample for testing

to detect current gonorrhea and chlamydial and trichomonal infections. Men who have had sex with another man and transgender women will be asked to provide a self-collected anal swab for further testing for chlamydia and gonorrhea at the study laboratory. Patrons or workers will be asked to collect these specimens in a restroom onsite. Interviewers will wait outside the restroom to receive the specimens. Participants will be given a phone number and an ID number with which they can collect the results of viral load, gonorrhea, chlamydia and trichomoniasis testing two weeks after participating.

Interviews with sex workers, MSM and transgender women will be conducted at all venues named as places where these populations can be found until the target number of respondents is reached. Our target is to interview 600 sex workers, 600 MSM and 200 transgender women at sites. However, a specific target cannot be determined until the end of the site verification phase. Interviewers will ask sex workers, MSM and transgender women about other venues where key populations can be reached. The list of venues will be expanded until the target number of key population participants has been reached.

The field supervisor will notify the venue owner and manager that the team will conduct the survey 1 or 2 weeks prior to recruitment and as soon as the team reaches the venue on the specific day and time. The coordinator will also be responsible for completing the Data Corrections Log (Appendix 11) and ensuring the appropriate information is collected prior, during and after the recruitment event.

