### **B. PLACE Analysis**

PLACE-based surveys will be analyzed using survey specific commands in SAS to account for the cluster design and weights. Weights will be constructed to produce unbiased population-based estimates and will be based on the following information: attendance at venues, attendance at specific venues or cluster size. Non-response bias will also be assessed by comparing proportion of missing data by key characteristics. We will generate population estimates for specific key indicators (Table 4).

One study objective is to estimate the proportion of key populations at each step of the HIV testing and treatment cascade, the basis for the LINKAGES Project. Table 4 includes indicators for the percent of HIV positive people who are aware of their status, the percent of those positive that are enrolled in HIV care, the percent who have initiated ART, the percent sustained on treatment for 12 months and the percent who are virally suppressed. Other indicators focus on coverage of HIV prevention activities such as HIV testing, STI screening, condom and lubricant distribution, information on HIV, AIDS, STI and safe sex and the percent of the population that has received a package of interventions.

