### C. Population Size Estimate Analysis

#### Population Size Estimation Analysis using PLACE

1. For each area that was mapped, we will estimate the number of sites in each area by type of site and type of key population at site
2. We will estimate the number of each type of key population at each type of site
3. We will provide a map of sites indicating the number of key populations at each
4. We will estimate the total number of key population member in each zone and in the sub-national areas included in the estimate
5. We will extrapolate the estimate to include areas not covered
6. We will estimate the number of key populations missing from the estimate based on findings from formative research
7. We will refine the size estimates based on mobility of key populations, visits to multiple venues, and variety in frequency of attendance
8. We will use the size estimates to calculate coverage for components of the comprehensive program for key populations

The following steps for size estimation will be followed:

1. Review data to confirm completeness of site lists and adequacy of estimates of the number of key population members at each site. Check the quality of the data by comparing the number of sites named and the number of times each was named with the number of reports naming a site from community informants. Check that there are sites named in every area included in the mapping activity. Confirm that the interviewers included members of each key population and that targets for type and number of community informants were reached. Review the list of sites that were not located and re-visit a random sample to confirm that the sites do not exist.
2. Calculate a point estimate for the number of each key population at each site based on the reported range provided. At each site, informants will be asked to estimate the maximum and minimum number of key populations at the site at a busy time.
3. Separate the estimates from sites that were initially identified as sites with key populations from sites that were not reported to have key populations. The rationale for treating the two types of sites differently is that they are sampled with different sampling fractions and the expected number of key populations at the sites reported to have key populations will be higher than at the other sites.
4. Add up the median number of key populations at each site for an initial crude estimate of the size of each population.

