**APPENDIX 4. Form C Patron and Worker Interview Questionnaire**

**FORM C: Patron and Worker Study Interview**

| PART I – COMPLETE BEFORE INTERVIEW |                                                                                |                                                                                                                                                                                      |
|------------------------------------|--------------------------------------------------------------------------------|--------------------------------------------------------------------------------------------------------------------------------------------------------------------------------------|
| NO.                                | QUESTION                                                                       | RESPONSE                                                                                                                                                                             |
| Q1                                 | Date:                                                                          | Day   Month   Year                                           |
| Q2                                 | Interviewer Code:                                                              | Interviewer Code:                                                                                                                            |
| Q3                                 | Type of social mobilizer present:                                              | No social mobilizer present during site visit 0
Sex worker 1
MSM 2
Trans woman (Male to female) 3
Trans man: (Female to male) 4
Person who injects drugs 5
Other 6 |
| Q4
A-C                          | Geographic Code of Site:                                                       | A. Province   B. District   C. Zone                          |

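### Step 4 sets conflicting venue and person selection rules and Form C does not record how a respondent was selected, so the listed inputs cannot support the promised unbiased PLACE weights

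*Protocol*

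**What the plan says.** All of this is current protocol text.

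- **Venues, rule A** (VI.C Step 4, selection of sites and events). Interviews and testing "will be performed in a sample of sites and events visited in the previous step". "Sites will be selected using a systematic fixed-interval sampling strategy with the probability of selection proportional to the size of the site". The frame is built from sites confirmed in Step 3, before the interval draw.
- **Venues, rule B** (VI.C Step 4, recruitment at venues). Key-population interviewing "will be conducted at all venues named as places where these populations can be found until the target number of respondents is reached". Respondents are asked for further venues: "The list of venues will be expanded until the target number of key population participants has been reached". No visit order is given.
- **Persons, rule A** (selection of sites and events). Where a mobilizer accompanies the team, "all people identified by social mobilizers as potentially people from key populations will be interviewed". Others are approached at random, with no fraction stated.
- **Persons, rule B** (recruitment at venues). Because venues should mostly be small, the default is to approach everybody present. Where that is not feasible, patrons and workers are each sampled systematically.
- **Weights** (VIII.B). "Weights will be constructed to produce unbiased population-based estimates and will be based on the following information: attendance at venues"; the other inputs named are attendance at specific venues or cluster size.
- **Size estimation** (VIII.C, PLACE, step 3). Key-population sites and other sites are handled separately because "they are sampled with different sampling fractions".
- **Data collected** (Appendix 4, Form C). Q3 records "Type of social mobilizer present". No item records whether this respondent was pointed out or approached at random, or how many people were present and approached.

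**The concern.** A design weight is the inverse of a selection probability. Here that probability has a venue part and a person part, and the protocol gives two incompatible accounts of each. The analyst must know which account applied at each venue and to each respondent. The weight inputs in VIII.B do not carry that information and Form C does not collect it.

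At stake are the HIV, STI and care-cascade estimates for key populations, which are central objectives, and the claim that they are unbiased. Section IV.B sets the protocol's own standard: ideally every member of the target population has a selection probability that is known and above zero. It also warns that recruiting people where they are most visible weakens representativeness.

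**Working it through.** **Plan's own figure.** The Luanda total reproduces as a sum of group expectations (VI.E): 600 + 600 + 200 + 600 = 2000. No precision calculation lies behind it, so the check below concerns the selection rules.

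**Venue level**

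1. Under rule A the probability for venue i is π_i = n × M_i / ΣM, where M_i is the reported busy-time crowd. Under take-all it is 1. Take assumed crowds of 20 and 150, which fall in the lowest and highest size classes of Form A2. The small-to-large ratio of base weights is 150/20 = 7.5 under rule A and 1 under take-all. The analyst must know which rule applied.
2. Under rule B there are two outcomes. If the target is met before the named venues run out, inclusion depends on visit order and on the yield of earlier venues. With no order fixed, that probability is undefined. If the target is not met, all named venues are visited but the list then grows by referral, and referral-added venues have no design probability.

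**Person level**

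Let v be the share of a venue's key-population members known to mobilizers and taken with certainty. Let f be the sampling fraction for the rest, and p_v and p_h the HIV prevalence in the two groups. Without route-specific weights:

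- mobilizer-known share of the sample = v / [v + (1 − v)f]
- estimated prevalence = [v·p_v + (1 − v)·f·p_h] / [v + (1 − v)f]
- true prevalence = v·p_v + (1 − v)·p_h

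The protocol gives none of v, f, p_v or p_h. For illustration only, p_v = 10.5% and p_h = 3.8%. These are the two ends of the range quoted for MSM in Luanda (section IV), assigned to the groups by assumption.

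| v | f | Mobilizer-known share of sample | True | Estimate |
|---|---|---|---|---|
| 0.5 | 0.10 | 91% | 7.15% | 9.9% |
| 0.5 | 0.25 | 80% | 7.15% | 9.2% |
| 0.5 | 0.50 | 67% | 7.15% | 8.3% |
| 0.5 | 1 | 50% | 7.15% | 7.15% |
| 0.3 | 0.10 | 81% | 5.8% | 9.2% |
| 0.3 | 0.25 | 63% | 5.8% | 8.0% |
| 0.3 | 0.50 | 46% | 5.8% | 6.9% |
| 0.3 | 1 | 30% | 5.8% | 5.8% |

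Worked line, v = 0.5 and f = 0.25: share 0.5/0.625 = 0.80; estimate (0.5 × 10.5 + 0.125 × 3.8)/0.625 = 9.2%.

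The sign is not fixed. If the two prevalences are swapped, the same line gives (0.5 × 3.8 + 0.125 × 10.5)/0.625 = 5.1% against 7.15%. If p_v = p_h, or if f = 1, there is no bias.

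**The case against.** **The default is to approach everyone.** The recruitment text expects small venues and a full approach. There f = 1, and certainty selection of mobilizer-identified people changes nothing. This stands. The person-level effect is confined to venues where others are subsampled, either because they are overfull or because the random-approach wording is followed. The two passages still conflict, and the venue-level problem is untouched.

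**Mixed selection can be weighted.** A reader might infer that combining size-proportional sampling, take-all and certainty selection makes weights impossible. The documents do not support that. Take-all at venues named for key populations and a size-proportional draw elsewhere are two ordinary strata, and step 3 of the size estimation already separates the site types. The obstacles are narrower: stopping at target with no order, venues added by referral, an unstated approach fraction and no record of route.

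**Weight formulas may sit in an SAP.** True, and the list in VIII.B need not be exhaustive. But no SAP can recover a route or an approach count that was never recorded.

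**Field limits are acknowledged.** Section IV.B presents PLACE as approximating probability sampling and lists its obstacles. That is fair, and it is a reason not to claim unbiased estimates in VIII.B.

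**The form can still change.** Step 1 provides for a pilot and protocol revision. This supports making the change before main fieldwork.

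**Conclusion.** The point holds in this form. The Step 4 selection passages must be reconciled. As written, the weight inputs in VIII.B together with Form C cannot deliver the unbiased population-based estimates promised.

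Over-representation of mobilizer-known people follows directly wherever others are subsampled. With half of members known to mobilizers, their share of the sample is 67% at a 1-in-2 fraction and 80% at 1 in 4. It does not arise where everyone is approached.

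A reader might go further and infer that HIV prevalence will be overestimated. The documents do not support this, because nothing in them links visibility to infection. The prevalence figures above rest on assumed values and would reverse under the opposite link. Nor is a lean towards venues visited early certain, since it arises only if the target is met before the named venues are exhausted.

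This should be settled before fieldwork: the weighting formula can be written later, but the route of selection cannot be reconstructed.

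**What to change.** 1. **One stratified rule for Step 4.** Visit venues named for key populations in a pre-randomised order, in replicates, stopping only when a replicate is complete. Select other venues by the size-proportional draw already described. State one within-venue rule covering mobilizer-identified people and everyone else.
2. **Record the route.** Add a Form C field (mobilizer-identified, or random/systematic) and a per-visit tally of numbers present and approached by route.
3. **Match the weights in VIII.B.** Base weight = 1 / (venue probability × within-venue probability for the route), adjusted for attendance frequency using C1, C2 and C4. C3 asks about meeting a new partner and is not an attendance item; C4 covers other places for one day only. If k of K random replicates are released, the venue probability in that stratum can be taken as k/K, given the number released.
4. **Referral-added venues.** Flag them as a separate non-probability group, since the weight in item 3 is undefined for them. Report estimates with and without them, and drop the word unbiased for any estimate that includes them.

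**Cost.** One form field, a short tally per visit and weighting code. Completing a replicate may overshoot the target slightly, and the weights will be somewhat more variable. Keeping venues named for key populations in their own randomised list, rather than drawing them in proportion to total crowd, avoids putting the 600/600/200 targets at risk.
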